# A multimodal intervention to optimise antimicrobial use in residential aged care facilities (ENGAGEMENT): protocol for a stepped-wedge cluster randomised trial

**DOI:** 10.1186/s13063-022-06323-8

**Published:** 2022-05-21

## Abstract

**Background:**

Inappropriate antibiotic use can cause harm and promote antimicrobial resistance, which has been declared a major health challenge by the World Health Organization. In Australian residential aged care facilities (RACFs), the most common indications for antibiotic prescribing are for infections of the urinary tract, respiratory tract and skin and soft tissue. Studies indicate that a high proportion of these prescriptions are non-compliant with best prescribing guidelines. To date, a variety of interventions have been reported to address inappropriate prescribing and overuse of antibiotics but with mixed outcomes. This study aims to identify the impact of a set of sustainable, multimodal interventions in residential aged care targeting three common infection types.

**Methods:**

This protocol details a 20-month stepped-wedge cluster-randomised trial conducted across 18 RACFs (as 18 clusters). A multimodal multi-disciplinary set of interventions, the ‘AMS ENGAGEMENT bundle’, will be tailored to meet the identified needs of participating RACFs. The key elements of the intervention bundle include education for nurses and general practitioners, telehealth support and formation of an antimicrobial stewardship team in each facility. Prior to the randomised sequential introduction of the intervention, each site will act as its own control in relation to usual care processes for antibiotic use and stewardship.

The primary outcome for this study will be antibiotic consumption measured using defined daily doses (DDDs). Cluster-level rates will be calculated using total occupied bed numbers within each RACF during the observation period as the denominator. Results will be expressed as rates per 1000 occupied bed days. An economic analysis will be conducted to compare the costs associated with the intervention to that of usual care. A comprehensive process evaluation will be conducted using the REAIM Framework, to enable learnings from the trial to inform sustainable improvements in this field.

**Discussion:**

A structured AMS model of care, incorporating targeted interventions to optimise antimicrobial use in the RACF setting, is urgently needed and will be delivered by our trial. The trial will aim to empower clinicians, residents and families by providing a robust AMS programme to improve antibiotic-related health outcomes.

**Trial registration:**

US National Library of Medicine Clinical Trials.gov (NCT04705259). Prospectively registered in 12th of January 2021.

**Supplementary Information:**

The online version contains supplementary material available at 10.1186/s13063-022-06323-8.

## Background

The World Health Organization (WHO) has declared antimicrobial resistance (AMR) to be a world-wide health crisis [1], with a global rise in antibiotic resistant organisms, resulting in significant increase in healthcare utilisation, morbidity and mortality [2]. In 2017, the WHO published its first ever list of antibiotic priority pathogens—12 groups of bacteria that pose the greatest threat to human health [1]. This burden of AMR is particularly high among elderly residents at long-term care facilities [3–5].

National point prevalence surveys have consistently demonstrated room for improvement in prescribing practices with approximately 10% of residents in Australian residential aged care facilities (RACFs)—long-term care facilities providing 24-h nursing services—using antibiotics at any given time [6, 7]. Data from the Pharmaceutical Benefit Scheme suggests that approximately 70% of RACF residents receive at least one course of antibiotics annually. Internationally, similar figures are reported with between 45 and 79% of residents from the USA, Canada and the UK receiving one or more antibiotics over a 12-month period [8, 9].

This is supported by a recent Australian study by Sluggett et al. that demonstrated an increase in both the prevalence and total consumption of antibiotics in RACFs over a 10-year period [10]. Studies indicate that a high proportion of these prescriptions (25-75%) are non-adherent with best prescribing guidelines and that treatment choice and duration are also frequently inappropriate [6].

There is a direct correlation between overuse of antibiotics and AMR [11]. RACFs are at particularly high risk of AMR as they provide long-term care to individuals who are often frail, with multimorbidity and live in close proximity, making them more prone to infections and subsequent antibiotic use. Furthermore, RACFs operate in a climate of tight resourcing and in many facilities there are no onsite doctors. Out of hours, medical advice is provided by practitioners who do not necessarily know the resident and may not have access to complete medical records. A large retrospective Australian study of antibiotic use in Australian RACFs found greater prevalence of out of hours medical practitioner services associated with greater antibiotic use [12].

RACFs have been identified as complex adaptive systems, with multiple influences on antimicrobial prescribing, including clinical staff, factors related to the facility and the resident and family wishes [13], all of which may play a role in inappropriate prescribing and the development of resistant organisms [14]. This is problematic given that RACF residents change care settings frequently, and resistant organisms may be transferred between the facility and acute care, increasing transmission of AMR [14].

A structured Antimicrobial Stewardship (AMS) model, incorporating multimodal interventions targeted at optimising antimicrobial use and resident outcomes in the RACF setting is urgently needed. AMS has been defined as “a systematic and coordinated approach to optimising antimicrobial use with the goals of improving patient outcomes, ensuring cost effective therapy and reducing adverse consequences of antimicrobial use, including AMR” [15]. Whilst in the Australian healthcare system AMS programmes have evolved significantly in acute care, and are now mandatory for hospital accreditation purposes, stewardship programmes in long-term care facilities are still evolving [16]. Recent Aged Care Quality standards require that data is used to monitor infections and resolution as part of the effectiveness of infection prevention and control programmes [17]. Facilities need to be able to provide evidence-based surveillance reports, with quality and risk interpretation of data [17].

### Key infection types and interventions to improve antibiotic use

The strongest evidence for inappropriate prescribing in the RACF setting relates to suspected urinary tract infections (UTIs), which account for up to 60% of antibiotic courses. Asymptomatic bacteriuria (ASB) (vs. symptomatic UTI) becomes more frequent with advancing age [18]. Antibiotic treatment for ASB has no benefits for the individual and does not reduce mortality, nor the incidence of symptomatic UTI [19]. Studies show that nearly half of antibiotic prescribing in RACFs is for ASB, or based on urine samples collected in residents whose symptoms are unlikely to be UTI related [19, 20].

Antibiotic consumption for other common conditions has also been identified as high and potentially inappropriate. These include respiratory tract infections (RTIs) and antibiotic prescribing in skin and soft tissue conditions. Together with UTIs these conditions account for approximately 90% of all infections (Table 1) [24]. Inappropriate treatment significantly increases the risk of antibiotic-related harm, including *Clostridium difficile* (*C. difficile*) infections and AMR. Ideally, interventions should aim to target all three areas to optimise impact. This is in line with the antibiotics on the WHO Watch list (i.e. those with high resistance potential), which should be targeted by AMS programmes [25].

**Table 1 Tab1:** Common conditions associated with sub-optimal antibiotic prescribing in RACFs

Conditions	Sub-optimal prescribing examples
Urinary tract infections	E.g. inappropriate prescribing in asymptomatic bacteriuria. Improving diagnosis and treatment of UTIs [5, 18, 21, 22] Inappropriate and widespread use of long-term prophylactic antibiotics for prevention of UTIs
Respiratory infections	E.g. antibiotic use in RTI, including bronchitis. RTIs are usually due to viruses and antibiotic use is inappropriate—there is a need for education and improving diagnosis [22, 23].
Skin and soft tissue	E.g. inappropriate treatment of conditions frequently confused with cellulitis such as venous stasis; inappropriate treatment of ulcer or wound bacterial colonisation [22]. Inappropriate use of topical agents [7]. There is a need for further education and improving diagnosis.

*UTI* urinary tract infection, *RTI* respiratory tract infection

Several interventions have shown positive results for improving antibiotic prescribing practices in the aged care setting [26–30]. Stewardship programmes incorporating educational elements have resulted in improved prescribing and reductions in unnecessary urine testing [26–29]. A systematic review by Davey et al. identified that dissemination of educational resources and audit feedback can assist with better prescribing of antimicrobials in the hospital setting [30]. Other interventions include implementation of site-specific guidelines, provision of telehealth services to facilitate timely advice from expert infectious disease clinicians [31] and use of decision support tools to guide prescribing [32]. A recently published systematic review highlighted studies that use several interventions have better outcomes than those using education only strategies [33]. Recently a multi-centre study by Nace et al. [18] reported a significant reduction of 17% in antibiotic use for asymptomatic bacteriuria through the delivery of a quality improvement intervention across 25 facilities in the USA. The study did not find any adverse events related to the intervention, with no differences in all-cause hospitalisations or resident mortality between the intervention and control groups [18].

A systematic review which specifically evaluated the impact of AMS on resident outcomes and health care utilisation also found interventions to be safe [34]. In this study, eight of 14 eligible studies reported a reduction in antibiotic prescribing [34]. Another review identified 19 studies that evaluated interventions to optimise antimicrobial use in the aged care setting [35]. Studies targeted either UTIs, RTIs or both. Only two studies demonstrated a significant decrease in antibiotic consumption, and no safety concerns were reported (e.g. change in hospitalisations or resident mortality) [35]. Most studies were conducted in the US long-term care facilities (*n*= 14), three in Europe and only one study in the Australian healthcare setting, which evaluated an educational intervention aimed at nursing staff. Studies were deemed to be at high risk of bias due to their design (i.e. not a randomised controlled study (RCT)) [35].

Whilst interventions have shown improvements in prescribing of antimicrobials, there are no studies to date which have evaluated the impact on antibiotic consumption (measured using defined daily doses [DDD]), resident impact (*C. difficile*, AMR and hospitalisations) and cost-effectiveness using a comprehensive set of multimodal interventions in a tailored bundle, as part of a stewardship programmes in the Australian RACF setting. Due to the variation in clinical governance, sociodemographic environments and the approach to medical diagnosis and treatment (e.g. in Australia physicians are generally not located onsite), a robust multicentre study in the Australian RACF context is needed. Furthermore, to date studies have lacked a rigorous study design with a high risk of bias. A study that delivers interventions using a stepped-wedge RCT design, whereby each facility can receive the intervention and act as its own control, could address previous deficiencies. Therefore, our research aims to identify the impact of a set of sustainable, multi-modal interventions, targeting three common areas of antibiotic prescribing using a stepped-wedge RCT design. It is our intention that the learnings from this research translate to sustainable improvements in resident outcomes at RACFs across Australia.

### Aims

To determine if the delivery of a bundle of multimodal interventions reduces antibiotic use in RACFs as measured by DDDs.To determine if this bundle has an impact on resident outcomes, including antibiotic-related harm, mortality and hospital admissions.To determine if this bundle is cost effective.

### Study hypothesis

Compared with routine care, implementation of a multimodal intervention bundle (AMS ENGAGEMENT) will be associated with a 20% reduction in DDD post trial intervention period.

The *null hypothesis* for this trial is there will be no change in DDD of antibiotics because of the trial intervention.

## Methods

This protocol was developed in accordance with the Standard Protocol Items: Recommendations for Interventional Trials (SPIRIT) Statement [36]. The completed SPIRIT Checklist is included in the Additional file 1. Reference was also made to CONSORT statement extension for cluster randomised trials and the recommended modifications for stepped-wedge designs [37].

### Design and setting

The study will be conducted in two parts, as summarised in Fig. 1:Part 1: Trial development. RACF recruitment and refinement of the AMS ENGAGEMENT intervention bundlePart 2: Stepped-wedge trial

**Fig. 1 Fig1:**
[figure not shown]
The trial schema outlining the development and stepped-wedge trial (intervention and control). AMS, antimicrobial stewardship; DDD, defined daily doses; RACF, residential aged care facility; NAT, Needs Assessment Toolkit

### Part 1: Trial development

#### Recruitment of RACFs

Eighteen RACFs will be recruited from South East Queensland, Australia, for this trial. Aged care service providers with facilities of 50 or more residents will be directly approached and invited by the research team through local pharmacy providers Service providers and facilities interested in participating will receive a letter of invitation to participate that details the participation requirements and the financial and in-kind support provided by the research team. Those that respond will also be invited to a meeting with members of the trial management committee to answer queries related to their participation in the trial.

#### Data collection

De-identified data will be collected from 18 RACFs for the same 6-month period (July to December 2020) on the following variables: antibiotics usage from pharmacy dispensing data, resident demographics from the RACF records and hospitalisations and mortality from hospital discharge summaries. This data will be used to calculate DDDs to form a reference base for safety monitoring.

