#### Exploratory outcome measures

Barriers and enablers to improving AMS practices in RACFs.

This study will also report outcomes in relation to most of the recently published Core Outcome Set for antimicrobial stewardship [41]. Antibiotic dispensing and resident data reported by RACFs will enable calculation of the total number of antimicrobial courses prescribed that are actually dispensed (incidence of antimicrobial use) per 1000 resident bed days; and days of therapy per 1000 resident bed days (rate of antimicrobial therapy). Infection-related mortality will also be reported (using before and after antibiograms). Appropriateness of antimicrobial prescribing will not be reviewed. No restrictions will be imposed on facilities for undertaking other education or activities related to medication prescribing and optimisation outside of the ENGAGEMENT bundle (e.g. routine facility pharmacist in-service sessions).

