### Data collection, management and monitoring

De-identified data will be provided by participating RACFs. Based on data sourced from pharmacy dispensing reports, infection control registers and electronic records systems, RACFs will provide monthly reports on antibiotic dispensing (as a proxy measure for consumption); suspected infections; number and types of pathology tests conducted relating to suspected UTIs or *C. difficile* infections; and details of resident hospitalisations, including admission and discharge dates, reason for hospitalisation and any additional medications or diagnoses related to the hospitalisation. Baseline data will be collected on residents’ demographics, co-morbidities (supplied annually to the Commonwealth Department of Health (i.e. the Aged Care Funding Instrument)), number of regular medications and current antibiotics. Antibiotics include all systemic antibacterials (the Anatomical Therapeutic Chemical (ATC) level J01) and topical antimicrobial agents.

An appropriately trained and authorised delegate at each facility will undertake data collection and reporting. This delegate will de-identify resident data prior to uploading to The University of Queensland’s secure Research Data Management platform, where it will be transferred into a REDCap© database. Only authorised users at each facility will be able to upload data using a unique username and password. The trial database will be stored securely on The University of Queensland network. A central coordinating centre (the Australasian Kidney Trials Network in the Centre for Health Services Research at The University of Queensland) will perform research data management and data cleaning. Access to research data will only be granted to staff involved in the cleaning and analysis of research data. The central coordinating centre will conduct on-site and remote monitoring at each RACF, on a quarterly basis or more frequently if needed, to ensure the accuracy and consistency of data collection and data management. This will include the comparison of source and trial data. The study design is open label so unblinding will not occur.

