### Trial safety monitoring

Trial safety will be monitored by an internal safety reviewer, who will be an infectious disease expert associated with the trial (but not a member of the TSC). This decision is based on findings of a recent trial of an AMS programme in 12 US RACFs [18] and a systematic review which included studies that evaluated the impact of AMS on health outcomes and health care utilisation [34]. Both studies found no significant differences in all cause hospital admissions or mortality between RACFs who received AMS-related interventions and those that did not. The appointment of an internal safety reviewer is also consistent with the Australian *National Statement on Ethical Conduct in Human Research (2007)* (National Statement) which “permits monitoring arrangements to be commensurate to the risk, size and complexity of the trial. The nature and extent of participant safety monitoring should be based on the assessment of the risks of the trial intervention(s) relative to standard care and the extent of knowledge about the IMPs/IMDs being tested. The sponsor’s plans for safety monitoring should be documented and continually reviewed and adapted during the trial, as real time assessments of safety data are performed.”

The Central Coordinating Centre (UQ) will prepare reports for the safety reviewer on resident hospitalisation, infection and mortality rates based on RACF monthly data submissions. Reports will be supplied to the safety reviewer, who will request further information, where applicable, on any significant deviations (≥1SD) from the trend.

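### Reference-period mortality is taken from hospital discharge summaries, which miss deaths in the facility and differ from the trial-period source; separately, antibiograms cannot yield infection-related mortality

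*Protocol article*

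**What the plan says.** Four places in the protocol article bear on where deaths come from.

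- **Part 1, Data collection.** Data are gathered from all 18 facilities "for the same 6-month period (July to December 2020"). Hospital admissions and deaths share one source: "hospitalisations and mortality from hospital discharge summaries". The stated purpose follows: "This data will be used to calculate DDDs to form a reference base for safety monitoring".
- **Data collection, management and monitoring.** For the trial period, "Based on data sourced from pharmacy dispensing reports, infection control registers and electronic records systems, RACFs will provide monthly reports". The items named are antibiotic dispensing, suspected infections, pathology tests and "details of resident hospitalisations, including admission and discharge dates, reason for hospitalisation". Deaths are not named.
- **Trial safety monitoring.** The coordinating centre "will prepare reports for the safety reviewer on resident hospitalisation, infection and mortality rates based on RACF monthly data submissions".
- **Exploratory outcome measures.** "Infection-related mortality will also be reported (using before and after antibiograms").

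All-cause mortality is a secondary outcome, compared between control and intervention periods. The section defining it names no data source.

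**The concern.** A discharge summary exists only for a resident who was admitted. A death in the facility leaves no such record, so the 2020 figure is a count of deaths in hospital and not an all-cause count. The trial-period figure comes from the facilities, which can also know of deaths on their own premises. The two series may therefore measure different things.

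This matters because the 2020 data are collected as a safety reference, and mortality is one of the three rates the safety reviewer receives. If reference and trial rates are set side by side, an apparent rise could be produced entirely by the change of source. The reviewer could not tell such a rise from real harm.

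The antibiogram wording is a separate fault. An antibiogram tabulates the susceptibility of isolates. It holds neither deaths nor causes of death, so the stated method cannot produce the stated measure.

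**Working it through.** The plan gives no mortality figure to reproduce. Its only design calculation, the 82% power, concerns DDDs and has no bearing here.

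**Step 1: sources side by side.**

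| Measure | Period | Stated source | Deaths it can show |
|---|---|---|---|
| Mortality, reference data | July to December 2020 | Hospital discharge summaries | Deaths in hospital only |
| Mortality, safety reports | Trial | Monthly facility submissions | Not specified; can include deaths in the facility |
| Infection-related mortality | Before and after | Antibiograms | None |

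**Step 2: size of the mismatch.** Let *m* be the true all-cause death rate, unchanged between periods, and *s* the share of deaths that occur in the facility. The reference then records (1 − *s*) × *m*. If the trial submissions count every death, they record *m*. The apparent rate ratio is

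*m* / [(1 − *s*) × *m*] = 1 / (1 − *s*).

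The documents do not give *s*; a range of 0.3 to 0.8 is assumed.

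- *s* = 0.3: 1 / 0.7 = 1.43
- *s* = 0.4: 1 / 0.6 = 1.67
- *s* = 0.6: 1 / 0.4 = 2.50
- *s* = 0.8: 1 / 0.2 = 5.00

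The ratio does not depend on *m*.

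**Step 3: what the reviewer might see.** This is an illustration only. Inputs from the sample size section are 18 facilities and 50 residents each. Annual mortality of 30% is an assumption. Expected deaths across the trial are 18 × 50 × 0.30 / 12 = 22.5 a month. Counts are taken as Poisson, the reference level as known, and the SD as the square root of the reference count. The query threshold of 1 SD is applied upward to the pooled monthly count.

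| *s* | Reference count, (1 − *s*) × 22.5 | Reference + 1 SD | Count that triggers a query | Probability of a query with no true change |
|---|---|---|---|---|
| 0 | 22.5 | 27.24 | 28 | 0.15 |
| 0.3 | 15.75 | 19.72 | 20 | 0.73 |
| 0.4 | 13.5 | 17.17 | 18 | 0.86 |
| 0.6 | 9.0 | 12.00 | 12 | 0.99 |
| 0.8 | 4.5 | 6.62 | 7 | 1.00 |

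With complete capture, about one month in seven would prompt a query by chance. With the source mismatch, most or nearly all months would.

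**Step 4: antibiograms.** No arithmetic applies. The secondary outcomes already include percent susceptibility of Enterobacteriaceae to four named agents, which is the kind of measure an antibiogram supports. Infection-related death needs a death record and a cause or diagnosis.

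**The case against.** The best defence is that the discharge-summary sentence is confined to Part 1, and that nothing obliges anyone to compare trial deaths with 2020 deaths. The safety section measures departures from a trend and does not say the 2020 level sets it. The Part 1 sentence, read literally, makes DDDs the reference base. This stands as a limit: the 1.4- to 5-fold figure is conditional on such a comparison and on an assumed share. It does not remove the point. Mortality is collected in that section, safety monitoring is the only use stated for the data, and the source named cannot give an all-cause rate.

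Three stronger readings are tempting, and the documents do not support them.

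- **A reader might infer that the trial's all-cause mortality outcome is unreliable.** It compares control with intervention periods inside the trial. No sentence ties it to discharge summaries or antibiograms, and trial-period safety rates are said to come from facility submissions.
- **A reader might infer that the monthly report has no field for deaths.** The published list is evidently condensed: it also leaves out occupied bed days, the denominator of the primary outcome. The safety section says the submissions yield mortality rates. That calls for confirmation and is not a defect.
- **A reader might infer that the query threshold, "on any significant deviations (≥1SD) from the trend", is an error.** For a stable, normally distributed rate it is crossed by chance in about 16% of readings upward and 32% in either direction. Crossing it only leads the reviewer to ask for more information. The article does not say whether rates are read by facility or for the whole trial. A low threshold is a trade-off between workload and sensitivity, and it does not affect how deaths are counted.

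The antibiogram remark may be a slip in a condensed sentence about a minor measure. That limits its weight, but as written it is wrong.

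**Conclusion.** Two statements need correcting. First, the 2020 mortality reference rests on a source that misses deaths in the facility and differs from the one used for trial safety reports, so the two rates are not comparable. The apparent inflation would be 1 / (1 − *s*), or 1.4 to 5 times for an assumed *s* of 0.3 to 0.8. That size assumes that trial reports count all deaths and that they are judged against the 2020 level; the documents settle neither. Second, antibiograms cannot supply infection-related mortality.

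The point reaches the safety reference and one measure listed with the exploratory outcomes. It does not reach the primary outcome, and it does not show bias in the all-cause mortality comparison.

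**What to change.** 1. Reconcile Part 1 Data collection, Data collection, management and monitoring, and Trial safety monitoring on one all-cause death source for both the 2020 reference period and the trial. Facility resident records, with date and place of death, would serve.
2. Confirm that the monthly report carries those items.
3. Under Exploratory outcome measures, replace the reference to antibiograms with a definition of infection-related death based on facility death records and hospital diagnoses. Keep antibiograms for the susceptibility outcome only.

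The cost is changes of wording and a re-extract of six months of facility death data. This assumes that facilities hold those data, which the documents do not state. If some do not, the 2020 figure should be labelled as deaths in hospital and not set against facility-reported mortality.

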#### Randomisation of RACFs

The 18 RACFs will be randomly assigned to an intervention starting time in a stepped-wedge RCT. The trial will be conducted across a 20-month observation period. The first month will be a control period for all sites; one site will transition from control to intervention each month for 18 months based on their randomisation; the final month will be an intervention period for all sites.

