### Sample size

Sample size was calculated based on the outcome of antibiotic consumption as measured by DDDs. For a trial to run over 20 months with a mean cluster size of 50 residents and a control event rate of 120 DDDs per 1000 resident days [22, 42], 18 RACFs will provide 82% power to detect a 20% reduction in DDDs, which has been demonstrated as feasible by other studies [28, 43] (although these studies have utilised other metrics to quantify antibiotic consumption). The power calculation is based on a conservative intra class correlation coefficient (ICC) of 0.012 and coefficient of variation of 0.3 [44].

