### Statistical analysis

The primary outcome is DDDs of antibiotics per 1000 occupied bed days. DDDs will be measured at the patient level monthly and analysed using a generalised linear mixed model for count data. The model will include fixed effects for intervention (AMS ENGAGEMENT vs control) and calendar time (randomised crossover times) and two random effects, one for variation among RACFs and a second to accommodate repeated measures over time on participants. Analysis will be by the intention-to-treat-schedule; that is, calendar time in the statistical model will be the randomised crossover times irrespective of whether crossover actually occurred at the pre-specified time. If there are discrepancies between randomised and actual crossover times, a supporting analysis will use the actual time that crossover occurred. Results will be expressed as rates per 1000 occupied bed days with 95% confidence intervals.

Data from the transition months will be reported but not included in the final analysis. All data will be analysed using SAS software (SAS Institute Inc., Cary, NC, USA). For the primary analysis, a *P* value less than 0.05 will be considered statistically significant. A statistical analysis plan will describe in detail the pre-specified analysis for all efficacy and safety outcomes and be available in the public domain before database lock.

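### Each facility's July–December 2020 antibiotic rate is collected but left out of the primary model; as a facility-level covariate it would add roughly 0 to 4 points of power

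*Protocol article*

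**What the plan says.** Under Part 1, Data collection, the protocol article describes de-identified data from 18 facilities over one common six-month window, July to December 2020, including antibiotic use from pharmacy dispensing. Its stated purpose is: "This data will be used to calculate DDDs to form a reference base for safety monitoring". It does not say that this is the only use, but no other section gives the data a second one.

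The Statistical analysis section sets out the primary model: "The model will include fixed effects for intervention (AMS ENGAGEMENT vs control) and calendar time", with random effects for facility and for participant. No pre-trial rate is named. The same section reports transition months but leaves them out of the final analysis.

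The Sample size section states that "18 RACFs will provide 82% power to detect a 20% reduction in DDDs", assuming a "mean cluster size of 50 residents and a control event rate of 120 DDDs per 1000 resident days" and a "conservative intra class correlation coefficient (ICC) of 0.012 and coefficient of variation of 0.3".

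Under Randomisation of RACFs, after one all-control month, "one site will transition from control to intervention each month for 18 months based on their randomisation".

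**The concern.** In this layout the first facility to cross contributes one control month, the second two, and so on; at the other end, the last facility contributes one intervention month. Where one side is that short, the facility's own level is poorly estimated, and the treatment estimate leans on comparisons between facilities. Those comparisons carry the between-facility variance.

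A pre-trial rate of the same outcome, from the same kind of source and before any intervention, can explain part of that variance. The data are already due to be collected. The margin is also thin: there are 18 clusters, stated power is 82%, and the protocol's own retention section expects that some sites may withdraw. The choice of covariate has to be fixed before outcome data are examined, which the promised analysis plan allows.

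**Working it through.** **Inputs from the protocol.** Control rate 0.12 and intervention rate 0.096 (a 20% reduction, difference 0.024); 50 residents per facility-month; coefficient of variation 0.3; ICC 0.012; 18 facilities crossing one per month over 20 months; significance level 0.05. Two-sided testing is my assumption.

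**Variance components.**
- Between-facility SD: τ = 0.3 × 0.12 = 0.036, so τ² = 0.001296.
- Facility-month sampling variance: σ² = 0.12 × 0.88 / 50 = 0.002112.
- Check: 0.001296 / (0.001296 + 0.1056) = 0.0121, which matches the stated ICC of 0.012. The plan therefore appears to treat the DDD rate as a proportion.

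**Method.** Generalised least squares for a cross-sectional stepped wedge, with a fixed effect for each month and one constant facility effect. Power = Φ(0.024/SE − 1.96).

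**The plan's figure.** The standard layout of 18 steps and 19 periods, with no month excluded, gives SE 0.00834 and power 82.0%, which reproduces the stated 82%.

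**The analysis as described.** With 20 months and each facility's transition month excluded, SE is 0.00882 and power 77.7%. Averaging the sampling variance over the two rates instead gives about 81%.

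**Adding the 2020 rate as a covariate.** A six-month facility mean has reliability R = τ²/(τ² + σ²/6) = 0.001296/(0.001296 + 0.000352) = 0.786. Let ρ be the correlation between a facility's true 2020 level and its true trial level. The covariate then leaves residual between-facility variance τ²(1 − ρ²R). The documents do not give ρ, so I show a range (transition months excluded):

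| ρ | Residual share of τ² | SE | Power | Gain (points) |
|---|---|---|---|---|
| 0 | 1.000 | 0.00882 | 77.7% | 0 |
| 0.5 | 0.803 | 0.00876 | 78.2% | 0.6 |
| 0.8 | 0.497 | 0.00858 | 79.9% | 2.2 |
| 0.9 | 0.363 | 0.00844 | 81.2% | 3.5 |
| 1 (no drift) | 0.214 | 0.00814 | 83.8% | 6.2 |

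**Entering the six months as control periods under one constant facility effect.** With no drift this also gives 83.8%. If ρ is below 1 but the model assumes it is 1, the model's SE stays at 0.00814 while the true SE grows:

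| ρ | True SE | Actual type I error | Power on true SE |
|---|---|---|---|
| 0.9 | 0.00857 | 6.3% | 80.0% |
| 0.8 | 0.00897 | 7.5% | 76.2% |
| 0.5 | 0.01009 | 11.4% | 66.2% |

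At 0.8 and below, this analysis has less power than leaving the data out (77.7%), and its error rate is too high. If the model allows a separate correlation between the two eras, validity is kept and the powers are those of the first table. If instead the correlation decays month by month across a gap of 8 to 11 months, the gain is 2.7 to 3.1 points at 0.99 per month, 0.4 to 0.6 at 0.95, and about 0.1 at 0.90. These gains are measured against a baseline that is itself lowered by the decay.

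**The gap.** The 2020 window closes in December, and randomisation began in September 2021 (Trial status). January to August 2021 is 8 unobserved months at the least. The first trial month is not dated.

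**The case against.** The strongest reply is that nothing here is wrong. The model is a conventional stepped-wedge model, the stated power rests on the trial months alone, and covariates are ordinary content for an analysis plan that is not shown. This stands in part: the point is about efficiency, not a contradiction. It remains worth making because the protocol does state both the purpose of the 2020 data and the model's fixed effects, and neither links the two.

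It can also be said that the data may not be comparable. The 2020 window lies in the COVID-19 period and covers half a seasonal cycle; the article does not say that the records are monthly or can be linked to trial residents; and it does not say outright that these 18 facilities are the randomised 18. The last is a fair reading of the recruitment and data-collection sections. The rest argues for the covariate form, which needs one rate per facility and lets the data set the weight of that rate.

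Three stronger readings are tempting, and none is supported:
- **That the gain is free.** The covariate uses one between-facility degree of freedom out of 18 facilities, and pooling the 2020 months under a constant facility effect can inflate type I error.
- **That the gain is 6 points.** This requires facility levels not to move across the gap, which the documents give no ground to assume.
- **That the resident data also collected, such as the "number of regular medications and current antibiotics", would guard against changing case mix.** They are described as baseline data, with no statement that they are refreshed for residents who enter later.

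**Conclusion.** The point holds as a modest improvement in efficiency. The 2020 facility rates have one named use, safety reference, and do not enter the primary model. As a covariate they raise power from 77.7% to about 78–81% for between-era correlations of 0.5 to 0.9, a gain of roughly 0 to 4 points over plausible values and 6 only in the limit. In this calculation the covariate does not lose power even at zero correlation, and it does not assume that facility levels stay constant.

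The figures rest on the plan's proportion-based variance with 50 residents per month, a linear rather than log-scale model, a large-sample normal test that does not charge the lost degree of freedom, and an unknown correlation. The absolute gain depends heavily on the first of these. With a Poisson variance on about 1520 resident-days per facility-month (50 residents × about 30.4 days), power would be near 100% with or without the covariate. Real DDD data are probably overdispersed relative to Poisson, so the true gain cannot be fixed from the protocol.

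**What to change.** In the statistical analysis plan, before outcome data are examined:

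1. Add each facility's log DDD rate for July to December 2020 as a fixed facility-level covariate in the primary model. Confirm that the 2020 facilities are the randomised ones and that the antibiotics and bed-day denominator are defined as in the trial. Say what is done if a facility has no 2020 rate.
2. If a supporting analysis enters the six months as control periods, specify a facility correlation that is era-specific or decays with time, not one constant facility effect. This analysis also requires the 2020 data to be available by month.
3. Describe the 2020 data as serving both safety reference and covariate adjustment.

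The cost is analysis-plan wording and one between-facility degree of freedom. The covariate needs no new data collection, no monthly breakdown of the 2020 data and no resident linkage.
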